#### Enrollment goals

Our enrollment goal for the primary non-inferiority aim (Aim 1) is 255 participants per arm. To achieve this goal, up to 2500 PMBB participants (cases and procedural controls) are expected to be contacted.

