#### Randomization

After at least 4 weeks, participants with an actionable finding (cases) who have not chosen to opt-out of receiving their results are randomized to receive their results by remote telehealth disclosure with a GC (Arm 1) or by a private ROR digital intervention (Digital-ROR) with the option to schedule a call with a GC at any time in the process (Arm 2). A permuted block design is used for randomization, stratifying by cancer or cardiovascular genes and sex.

Randomized participants are sent the Step 2 Letter by MyPennMedicine portal (MPM), encrypted email or mail informing them that an actionable genetic finding that could potentially impact their health has been identified (Supplemental Fig. 2). The letter includes how they will receive their actionable results (according to their randomization), the next steps for receiving results and that they can still elect to NOT receive results. Procedural controls do not receive the Step 2 Letter, but any who opt-out of results after the Step 1 Letter has their decision recorded in case they are found to have an actionable result with additional sequencing or analysis.

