#### Uptake of results and patient reported outcomes (aims 1 and 2)

Theoretically informed patient-reported cognitive, affective and behavioral outcomes of genetic services are collected at baseline (T0), 2–7 days post-disclosure (T1) and at 6 months (T2).

Knowledge of genetic disease (primary non-inferiority outcome) is evaluated at all time points (T0-T2) using an adapted version of the KnowGene Scale, a 16-item scale administered to patients after genetic testing and/or genetic counseling to measure their understanding of the health implications of genetic test results [111]. It includes health implications to oneself as well as relatives. This measure covers penetrance, actionability, limitations of current technology, and monogenic inheritance patterns. Items 3, 5, 13 and 15 were excluded as they are not relevant to return of actionable results. Additionally, 4 items evaluating understanding of the difference between research and clinical testing and utilized in the RESPECT2 study were added to create a final scale of 16 items. This adapted scale has had good internal consistency in our pilot and related studies (Cronbach’s α = 0.63–0.83) [79, 112]. Perceived risk of cancer and cardiovascular disease (T0-T2) is evaluated with a numerical scale (risk 0-100%) and an 5-point verbal scale (much lower than average risk to much higher than average risk) as utilized in our related studies. The 8-item Attitudes Toward Genetic Testing scale is assessed at baseline to understand perceptions of genetic testing and to assess informed choice in combination with genetic knowledge and decisions to proceed with testing, as previously utilized in the multi-dimensional measure of informed choice and our related research (Cronbach’s α = 0.73) [113–115]. *Reactions to genetic information* are assessed with multiple instruments that evaluate psychological distress, adjustment and satisfaction. (a) Disease-specific distress (primary non-inferiority outcome) is measured at all timepoints (T0-T2) using the 8-item version of the Revised Impact of Events Scale (RIES) [94, 116–121], evaluating intrusive and avoidant thoughts regarding cancer and cardiovascular disease separately. The 8 item scale has strong internal consistency in related studies and our pilot study (Cronbach’s α = 0.70–0.92) [122, 123]. (b) *General anxiety and depression* are assessed by the respective 4-item short Patient Reported Outcomes Measurement Information System (PROMIS) scales (Cronbach’s α = 0.88 and 0.86) [79, 124]. (c) *Satisfaction with genetic services* (T1 only) will be assessed with a 14-item satisfaction with communication scale, and adapted for telehealth and digital disclosure, evaluating participants’ experience with high internal consistency in our related studies (Cronbach’s α = 0.73–0.85) [112, 114, 125] (d) *Multidimensional responses to genetic testing*, including positive responses and uncertainty, are assessed at T1 and T2 using the 20 items from the Multi-dimensional Impact of Cancer Risk Assessment Questionnaire (MICRA) with strong internal consistency in our pilot study by subscales (Cronbach’s α = 0.77–0.85) [79, 126]. (e) Decisional regret (T1, T2) is assessed using with the 5-item validated Decision Regret Scale used in genetic studies [127, 128]. This scale has had strong internal consistency in our pilot study (Cronbach’s α = 0.86) [79]. *Use of genetic information* includes uptake of receipt of actionable research results and other health and communication behaviors. (a) *Uptake of research results (secondary non-inferiority outcome)* will be assessed as completion of a remote telehealth disclosure session with a GC (either arm) or as viewing results in digital-ROR (digital arm). Other secondary uptake behaviors include uptake of supplemental digital education (Aim 2a), assessed as completion of pre-disclosure digital education or Chat 1, actively opting-out of receipt of research results after the Step 1 or Step 2 Letter (Aim 2b), completion of confirmation testing, and completion of clinical genetics follow-up, either by documentation in the EHR or self-report by those who are no longer in the local area. (b) Risk reducing behavioral intention (T1 only) and performance (T2) will be assessed with a close-ended and open –ended items given a lack of established measures and the wide range of potential medical management options depending on the individual gene. General health status and risk modifying behaviors (e.g. diet, exercise, tobacco and alcohol use) will be assessed at baseline and at T2 with items utilized in BRFSS and related studies [73, 125, 129]. Additionally, gene-specific medical management or risk reducing screening and interventions will be abstracted from medical records. (c) Communication of genetic test results includes communication intent (T1 only) and performance (T2) assessed using a 3-item measure of intent and communication to assess intent to share genetic test results with health care providers, family members and other third parties utilized in related research [85–87]. 

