### Data analysis plan

#### Primary non-inferiority analyses

We hypothesize that disclosure of actionable results by digital-ROR, with access to a GC, can provide non-inferior short-term and longitudinal cognitive, affective, and behavioral outcomes, and lower costs. Primary effectiveness outcomes include: post-disclosure knowledge and cancer or cardio disease-specific distress. We will test whether the receipt of results differ between arms as a secondary analysis. Receipt of results is considered a health behavior. For the 2 primary analyses, we will apply non-inferiority tests to examine if access to digital-ROR is non-inferior to GC disclosure. We will conclude non-inferiority if the upper bound of the randomization effect 97.5% one-sided confidence interval [CI] for cross-sectional T1 responses do not cross a -0.45 standardized difference threshold (i.e., margin) for knowledge and a 0.2 standardized threshold (i.e., margin) for disease-specific distress in the direction that would suggest that digital-ROR is worse. A standardized difference is the difference after variables are scaled to have standard deviation (SD) one with respect to baseline SD. We based the margins on what might be considered clinically relevant effects given our pilot data. We will use intention-to-treat approaches, comparing randomized arms, with confirmation by per-protocol analyses (i.e. restricting sample to those who properly used the method of disclosure as assigned). We will only declare non-inferiority if both intention-to-treat and per-protocol analyses are consistent, as recommended [133, 134]. For the secondary outcome receipt of results, we will examine non-inferiority of proportions. We will declare non-inferiority if the upper bound of the randomization effect 95% one-sided confidence interval for receipt of results is < 10% in the direction that favors usual care. Since all participants will have the option to speak with a GC, we will conduct secondary as-treated analyses (i.e. based on whether genetic counseling was actually received in both arms).

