We chose *n* = 255/arm so we could conclude non-inferiority of digital-ROR if randomization effects comparing the digital arm to GC arms at T1 do not show clinically relevant worsening in the web arm. We chose a margin of -0.45 standard deviation units for knowledge and 0.20 for distress since they are considered modest changes in behavioral research, and they are consistent with our pilot data. In preliminary data from our pilot study, the baseline knowledge standard deviation was 2.86 points. A -0.45 standard deviation difference * (times) 2.86 = -1.29 points. A 1.29 point worsening in the knowledge scale would not be considered a meaningful difference. For disease specific distress, the baseline standard deviation was 9.31 points. A 0.20 standard deviation difference * (times) 9.31 = 1.86 points. Again, a 1.85 unit worsening in the distress scale would not indicate a clinically relevant change.

Table 4 demonstrates potential allowable non-inferiority differences. We chose 2.5% Type I error by applying a Bonferroni correction to a 5% Type I error rate with 2 comparisons (5%/2 = 2.5%). We calculated power using simulations in R with confirmation using PASS 11 software. For our secondary outcome of receipt of results, we will declare digital-ROR effect non-inferior if the upper bound of the 95% one-sided confidence interval effect is less than 11% in a direction that would favor usual care. This has an approximate 5% non-inferiority Type I error rate and > 80% power over a range of plausible differences given our preliminary data (e.g. >55% promising rate seen in preliminary data versus < 44% discouraging rate, *n* = 255/arm). We assumed a binomial pooled standard error estimator. We do not correct for multiple testing of secondary outcomes.

**Table 4 Tab4:** Estimated non-inferiority power, 2.5% Type I error (1-sided), number = 255/group (510 total)

Variable	Biobank Wave 2 Pilot Study	Non-inferiority difference allowed	Non-Inferiority Type 1 Error Rate and Power
Knowledge	T1 Mean 13.20, SD = 2.59 GC arm T1 Mean 12.50, SD = 2.12 Web arm Web minus GC effect = -0.7 Baseline standard deviation = 2.86	-0.45 SD units * 2.86 base SD = -1.29 point margin	2.5% Type I error rate > 80% power with − 0.7 pilot data effect > 99% power with 0 point effect

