#### Interim analyses

We conducted an interim analysis after 100 people per arm had been enrolled and completed the T1 post-disclosure survey (200 total who have completed the T1 survey). We constructed the interim analysis to protect the Type I error rate. We did not pause the study based on the interim analysis.

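### The same 255 per arm serves as the denominator for receipt of results and as the number with T1 scores; at about 55% uptake it cannot be both

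*Protocol article*

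**What the plan says.** All references are to the protocol article.

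- **Enrollment goals:** "Our enrollment goal for the primary non-inferiority aim (Aim 1) is 255 participants per arm". It does not say whether these are people randomised or people with T1 data.
- **Randomization:** "participants with an actionable finding (cases) who have not chosen to opt-out of receiving their results are randomized". Randomisation therefore comes before anyone receives a result, and the letter sent afterwards still lets people decline. Non-response procedures provides for those who never come forward.
- **Uptake of results and patient reported outcomes:** the patient-reported outcomes "are collected at baseline (T0), 2–7 days post-disclosure (T1) and at 6 months (T2"). Knowledge and disease-specific distress at T1 are the primary outcomes.
- **Sample size justification for aim 1, receipt of results:** the planning values are ">55% promising rate seen in preliminary data versus < 44% discouraging rate, *n* = 255/arm", with stated power above 80%.
- **Table 4, T1 outcomes:** the title is "Estimated non-inferiority power, 2.5% Type I error (1-sided), number = 255/group (510 total"). Stated power for knowledge is >80% at -0.7 and >99% at 0. For distress it is >95% at -0.22 and >90% at 0.
- **Interim analyses:** the interim look came "after 100 people per arm had been enrolled and completed the T1 post-disclosure survey".
- **Background:** uptake elsewhere was 48–86%, and about 50% in biobank studies.

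**The concern.** Receipt of results is counted over everyone randomised. A T1 score can exist only for someone who has had a disclosure. If roughly 55% of those randomised receive results, the randomised group and the group with T1 scores differ by nearly a factor of two, yet both calculations use 255 per arm. The article states no inflation for non-receipt or for declining the surveys, which need their own consent (Ethics approval).

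What is at stake is the primary power statement. If 255 is the number randomised, the trial has much less power at the pilot's own knowledge effect than the article claims, and a failed or marginal result would be read against the wrong expectation. If 255 is the number with T1 data, the number to be randomised is not given, and the receipt calculation rests on too small a denominator.

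**Working it through.** **Inputs (Table 4 and the sample size text).** One-sided alpha is 0.025 for the primary outcomes. The knowledge margin is 0.45 × 2.86 = 1.287 points, with T1 SDs 2.59 and 2.12. The distress margin is 0.20 × 9.31 = 1.862 points, with T1 SDs 5.72 and 6.42. For receipt, the rate is 0.55 in both arms, alpha is one-sided 0.05, and the margin is 11 points in the sample size text (10 points in the analysis section).

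**Formulas.** For a mean, SE = √((SD₁² + SD₂²)/n) and power = Φ((margin − true deficit)/SE − 1.96). For receipt, SE = √(2 × 0.55 × 0.45/n) and power = Φ(margin/SE − 1.645).

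**Step 1: reproduce the plan at n = 255 per arm, all observed.**
- Knowledge: SE = √(11.2025/255) = 0.2096. At -0.7, Φ(0.587/0.2096 − 1.96) = 80.0% (80.4% with the printed margin of 1.29). At 0 it exceeds 99.9%.
- Distress: SE = √(73.9348/255) = 0.5385. At 0, Φ(1.862/0.5385 − 1.96) = 93.3%. At -0.22, Φ(2.082/0.5385 − 1.96) = 97.2%.
- Receipt, 11-point margin: SE = √(0.495/255) = 0.0441, power 80.3%.

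The stated figures are recovered, so both calculations treat 255 per arm as fully observed. The baseline SDs in place of the T1 SDs do not recover Table 4: knowledge at -0.7 is 64%, and distress is 71% at -0.22 and 62% at 0.

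**Step 2: suppose 255 per arm are randomised.** The number with T1 data is 255 × uptake, before survey refusal.

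| Uptake | T1 n per arm | Knowledge at -0.7 (stated >80%) | Knowledge at 0 (stated >99%) | Distress at -0.22 (stated >95%) | Distress at 0 (stated >90%) |
|---|---|---|---|---|---|
| 86% | 219 | 73.7% | >99.9% | 94.8% | 89.3% |
| 55% | 140 | 54.6% | 99.5% | 81.7% | 72.7% |
| 48% | 122 | 49.1% | 98.9% | 76.3% | 66.7% |

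At 140 per arm the SEs are √(11.2025/140) = 0.283 and √(73.9348/140) = 0.727. Simulation with arm-specific SDs gives 54.0% for knowledge at -0.7 and 81.6% for distress at -0.22.

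**Step 3: suppose 255 per arm have T1 data.** Table 4 is then correct. The number randomised is 255/0.55 = 464 per arm (255/0.86 = 297 and 255/0.48 = 532 at the ends of the range). With 464 per arm, the receipt SE is √(0.495/464) = 0.0327. Power is 95.8% at the 11-point margin and 92.2% at the 10-point margin.

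**The case against.** The best defence is that 255 means T1 completers. The sample size text chooses n for effects at T1, the interim look was counted in completed T1 surveys, and only the surveys need new consent, so enrolment can naturally mean survey participants. On that reading Table 4 is right and the receipt claim is conservative. This has real support, but it does not settle the matter: the receipt calculation prints 255 as its own denominator, and the primary analysis compares arms as randomised.

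Multiple imputation (Missing data) might be said to restore n. It can use only what the other observed variables predict; it does not replace scores from people who never had a disclosure. Table 4 is recovered only with 255 observed.

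It may also be said that an article condenses. Here, though, one printed n serves two incompatible counts, which is a conflict between stated numbers.

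Three stronger inferences are tempting and not supported:

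- **That one set of stated power figures must be false.** Under the completer reading every power statement holds; only the n attached to receipt is wrong.
- **That 140 per arm is a ceiling under the randomised reading.** The article writes ">55% promising rate seen in preliminary data versus < 44% discouraging rate", so 55% is a lower planning value, and uptake up to 86% is cited.
- **That Table 4 errs by ignoring a joint success rule.** The article says "We will only declare non-inferiority if both intention-to-treat and per-protocol analyses are consistent, as recommended", but Table 4 claims no power for that rule and no per-protocol exclusion rate is given. The Bonferroni split fits a separate claim for each primary outcome.

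**Conclusion.** The point holds as a conflict over what 255 counts. Either the T1 calculation or the receipt calculation uses the wrong n, and the article does not settle which.

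If 255 per arm are randomised, three of the four Table 4 figures fail at 55% uptake, and the same three still miss at 86%, the two distress figures only narrowly. Knowledge at zero difference stays at about 99% or more throughout. If 255 per arm are T1 completers, the primary power is as stated, and receipt power is understated, with the wrong n beside it.

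These sizes assume equal uptake in both arms, the Table 4 T1 SDs, no loss from survey refusal (no rate is documented; any refusal lowers the T1 numbers further), and no information regained through imputation or covariates.

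**What to change.** In Enrollment goals, the sample size justification for aim 1 and Table 4, state whether 255 per arm counts randomised participants or T1 completers, and give both expected numbers.

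- **If completers:** state the expected number randomised (about 464 per arm at 55% uptake, before survey refusal) and recompute receipt power on it. The 10-point and 11-point receipt margins differ between sections, so say which one the recalculation uses.
- **If randomised:** restate Table 4 on the expected number with T1 data.

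In either case, show the affected power over the cited 48–86% uptake range. The cost is rewording and one recomputed table. Under the randomised reading some stated power figures fall. No extra enrolment is requested, and no outcome, margin or analysis has to change.

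### Table 4's power for knowledge at the pilot effect is that of one intention-to-treat test on 255 per arm, not of the two-analysis rule by which non-inferiority is declared

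*Protocol article*

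**What the plan says.** Two parts of the protocol article bear on this.

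- **Decision rule** (Data analysis plan, Primary non-inferiority analyses). "We will only declare non-inferiority if both intention-to-treat and per-protocol analyses are consistent, as recommended". The per-protocol analysis means "restricting sample to those who properly used the method of disclosure as assigned".
- **Power** (Sample size justification for aim 1, Table 4). For knowledge at T1 the pilot inputs are "T1 Mean 13.20, SD = 2.59 GC arm T1 Mean 12.50, SD = 2.12 Web arm" and "Web minus GC effect = -0.7". The baseline SD of 2.86 times -0.45 gives a margin of -1.29 points. At a one-sided 2.5% level and 255 per group the table states "2.5% Type I error rate > 80% power with − 0.7 pilot data effect", and more than 99% at zero effect. For distress it states more than 95% at -0.22 and more than 90% at zero effect.

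Under Enrollment goals: "Our enrollment goal for the primary non-inferiority aim (Aim 1) is 255 participants per arm". This is the number used in the power table. The sample size section does not mention the two-analysis requirement, a per-protocol fraction or an allowance for one.

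The section on Arm 2 (digital-ROR) lets participants schedule a counselor disclosure session if they prefer.

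**The concern.** A claim of non-inferiority needs two successes, one of them on a subset of the randomized participants. The printed power appears to be that of one test on everyone. The power to meet both criteria cannot exceed the power of the weaker test, and it falls as the per-protocol set shrinks.

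For knowledge at -0.7 the single-test figure sits almost exactly on 80%, so nothing is in reserve. If the trial fails to declare non-inferiority on knowledge, readers will judge that against the printed power. Part of the failure could come from a smaller per-protocol set and be mistaken for evidence against digital disclosure.

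**Working it through.** **Inputs from Table 4 and the sample size section.** 255 per arm; T1 SDs 2.59 (GC) and 2.12 (web); effect -0.7; margin 0.45 × 2.86 = 1.287, printed as 1.29; one-sided 2.5%, so z = 1.96.

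**Step 1: reproduce the stated figure.**

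SE = √((2.59² + 2.12²)/255) = 0.2096

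Power = Φ((1.287 − 0.7)/0.2096 − 1.96) = Φ(0.841) = 80.0%; with 1.29 it is 80.4%.

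Distress reproduces in the same way: SE = √((5.72² + 6.42²)/255) = 0.5385 and margin 0.20 × 9.31 = 1.862. This gives Φ((1.862 + 0.22)/0.5385 − 1.96) = 97.2% at -0.22 and 93.3% at zero. All the printed figures therefore match one test on the full sample.

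**Step 2: joint power.** The per-protocol set is nested in the intention-to-treat set. The two estimates are treated as bivariate normal with correlation SE(ITT)/SE(PP), and both must clear the margin. Assumptions: 255 T1 responses per arm, the same SDs and the same true effect in both sets. The documents give no exclusion rate, so a range is shown.

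Worked case, 10% of Arm 2 excluded (229.5 left):
- SE(PP) = √(2.59²/255 + 2.12²/229.5) = 0.2142
- correlation = 0.2096/0.2142 = 0.978
- ITT limit 0.841; PP limit (0.587/0.2142) − 1.96 = 0.780, or 78.2% alone
- both: 76.6%

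Knowledge at -0.7, joint power:

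| Excluded | Margin 1.287 | Margin 1.29 |
|---|---|---|
| 5% of Arm 2 | 77.9% | 78.3% |
| 10% of Arm 2 | 76.6% | 77.1% |
| 20% of Arm 2 | 74.1% | 74.6% |
| 30% of Arm 2 | 71.3% | 71.7% |
| 10% of each arm | 73.7% | 74.1% |
| 20% of each arm | 68.4% | 68.9% |

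A simulation with t-based limits at margin 1.29 gave 74.2% with 230 per arm and 68.7% with 204 per arm, in line with the last two rows.

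**Step 3: unequal effects in the two sets.** Suppose 10% of Arm 2 take counselor disclosure and respond like Arm 1 (margin 1.287).
- If the intention-to-treat effect is -0.7, the per-protocol effect is -0.7/0.9 = -0.778, and joint power is 66%.
- If the per-protocol effect is -0.7, the intention-to-treat effect is -0.7 × 0.9 = -0.63, and joint power is 78%.

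At 20% crossover the two cases give 47% and 76%.

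**Step 4: the other rows of Table 4.**
- Knowledge at zero effect: joint power stays above 99.9% even with 30% lost from both arms.
- Distress at zero effect, margin 1.862, Arm 2 losses only: 91.1% at 10% and 89.1% at 20%, against a stated figure above 90%. With the rounded margin of 1.9 it is 90.3% at 20%.

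**The case against.** The best defence is that Table 4 contains no arithmetic error and never claims to show joint power. The sample size section ties 255 per arm to the randomization effect at T1, which is the intention-to-treat contrast. The rule asks only that the two analyses be consistent, a word left undefined, and it describes the per-protocol analysis as confirmation. Part of this stands: the figures are correct for one test, and a second full-margin test is an inference. It is still the natural reading of a rule that makes the declaration depend on both analyses. The article prints both the rule and a power figure that does not belong to it, so this is more than detail left to a fuller document.

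A reader might infer stronger versions, which the documents do not support:

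- **That any single exclusion matters.** Losing one Arm 2 participant moves knowledge power to 79.5% or 79.9%, depending on the rounding of the margin. That is negligible.
- **That the per-protocol set must be well below 255, in both arms.** Arm 2 is defined as digital return with a counselor call available at any time, so a call alone need not breach protocol. Only those who take disclosure from a counselor instead of the website plausibly leave the set. No crossover route is described for Arm 1, and a participant there who answers the post-disclosure survey has normally had the assigned session.
- **That the sponsor expects frequent counselor requests.** The limitations section says pilot data suggest high interest in digital options and treats frequent requests as a contingency.
- **That dilution pulls power to 66% or 47%.** Those values fix the intention-to-treat effect at -0.7. The mirror case gives 78% and 76%, and nothing in the documents chooses between them.
- **That the trial is underpowered in general.** The Discussion hypothesizes equal or improved outcomes, and at zero effect knowledge power is untouched.

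**Conclusion.** The point holds, at moderate size. The printed power for knowledge at -0.7 is the power of one full-sample intention-to-treat test, with no slack, and not the power to declare non-inferiority under the stated rule.

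With Arm 2 losses of 5% to 30%, the same effect in both sets and 255 T1 responses per arm, joint power is about 78% down to 71%. It would be about 74% or 68-69% if 10% or 20% were also lost from Arm 1. Dilution at 10% crossover widens the range to 66-78%.

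The problem lies mainly in the -0.7 row. Knowledge at zero effect is unaffected, and distress at zero effect slips to about 89% only at 20% Arm 2 loss, with the unrounded margin. All of these sizes rest on assumed exclusion rates and on reading consistency as both analyses meeting the margin.

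**What to change.** Keep 255 per arm and the two-analysis rule. In Table 4, label the present figures as intention-to-treat only. Next to them, print the joint intention-to-treat and per-protocol power from the existing R simulation, for knowledge and distress, over a stated range of per-protocol fractions in each arm. An example entry is about 77% for knowledge at -0.7 with 10% of Arm 2 excluded. State whether the effect is assumed equal in the two sets, and say that consistency means both analyses meet the margin, if that is what is intended.

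The cost is a rerun of the simulation and a revised table. The stated knowledge power becomes slightly less favourable. No participants are added and conduct does not change.
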